## Abstract

**Background:**

Total hip arthroplasty is one of the most commonly performed surgical procedures worldwide. There are a number of surgical approaches for total hip arthroplasty and no high-level evidence supporting one approach over the other. Each approach has its unique benefits and drawbacks. This trial aims to directly compare the three most common surgical approaches for total hip arthroplasty.

**Methods/design:**

This is a single-centre study conducted at Western Health, Melbourne, Australia; a large metropolitan centre. It is a pragmatic, parallel three-arm, randomised controlled trial. Sample size will be 243 participants (81 in each group). Randomisation will be secure, web-based and managed by an independent statistician. Patients and research team will be blinded pre-operatively, but not post-operatively.

Intervention will be either direct anterior, lateral or posterior approach for total hip arthroplasty, and the three arms will be directly compared. Participants will be aged over 18 years, able to provide informed consent and recruited from our outpatients. Patients who are having revision surgery or have indications for hip replacement other than osteoarthritis (i.e., fracture, malignancy, development dysplasia) will be excluded from the trial.

The Oxford Hip Score will be determined for patients pre-operatively and 6 weeks, 6, 12 and 24 months post-operatively. The Oxford Hip Score at 24 months will be the primary outcome measure. Secondary outcome measures will be dislocation, infection, intraoperative and peri-prosthetic fracture rate, length of hospital stay and pain level, reported using a visual analogue scale.

**Discussion:**

Many studies have evaluated approaches for total hip arthroplasty and arthroplasty registries worldwide are now collecting this data. However no study to date has compared these three common approaches directly in a randomised fashion. No trial has used patient-reported outcome measures to evaluate success. This pragmatic study aims to identify differences in patient perception of total hip arthroplasty depending on surgical approach.

**Trial registration:**

Australian New Zealand Clinical Trials Registry, ACTRN12617000272392. Registered on 22 February 2017.

**Electronic supplementary material:**

The online version of this article (10.1186/s13063-017-2368-7) contains supplementary material, which is available to authorized users.

## Background

Total hip arthroplasty for osteoarthritis has long been demonstrated to be a cost-effective treatment for osteoarthritis of the hip with improvements in pain, improved function and quality of life [1–3]. Many studies have demonstrated the effectiveness of total hip arthroplasty as an intervention in terms of patient-reported outcome measures [4, 5]. Osteoarthritis is the condition with the single largest expenditure of the Australian health budget, with $1.64 billion spent on osteoarthritis in 2008–09, 77% of which was for surgical procedures relating to osteoarthritis [6].

Total hip arthroplasty is the most common operative intervention for the treatment of severe osteoarthritis, with 32,306 primary total hip arthroplasties reported in 2014, 88.5% of which were for osteoarthritis. The Australian Orthopaedic Association National Joint Replacement Registry reports that this rate is increasing, with a 5.4% increase in the annual amount of total hip replacements in 2014 compared with the previous 12 months [7]. Studies in the USA have estimated an almost 200% increase in demand for total hip arthroplasty on current rates by 2030 [8].

There are a number of different surgical approaches to total hip arthroplasty, with the most common ones performed including the direct lateral (Hardinge), posterior and direct anterior approaches.

### Posterior approach

This approach is the most common approach for total hip arthroplasty worldwide today, made popular by Moore in 1959 [9]. This approach allows excellent visualisation of the femoral shaft with reduced risk of femoral fracture but involves detachment of the short external rotators of the hip. Posterior capsulotomy is a theoretical risk for dislocation in this approach and the sciatic nerve is also at risk [10]. The abductor muscles are not incised; therefore, the incidence of gait disturbance (Trendelenburg gait) is reduced compared with the Hardinge approach. A Swedish joint registry study showed slightly better pain and functional scores for patient-reported outcome measures in patients who underwent a posterior approach compared with a direct lateral approach [11].

### Direct lateral approach

This was first described by Hardinge in 1982 [12]. This approach requires bisection of the anterior half of the periosteum overlying the greater trochanter and reflection of the gluteus medius and minimus muscles. The superior gluteal nerve and artery are at risk if the approach is extended proximally. The advantage of this approach is that it can be extended distally for greater exposure of the femur where necessary and theoretically has a lower dislocation risk than the posterior approach. Gluteal tendon splitting can lead to a post-operative Trendelenburg gait.

### Anterior approach

This approach to the hip joint was initially described by Hueter [13, 14] and later popularised by Smith-Petersen [15]. It utilises the anatomic internervous plane between the superior gluteal nerve laterally and femoral nerve medially and has recently been popularised for total hip replacement [16], but its first reported use for total hip replacement dates back to 1947 in France, by Judet and colleagues [17]. Studies have suggested higher rates of dislocation in patients who underwent a posterior approach for their total hip arthroplasty [18]. The neurovascular plane for the anterior approach is between the superior gluteal nerve and the femoral nerve. In some reports, patients who have undergone an anterior approach for total hip arthroplasty have shorter hospital stays than those who have undergone a posterior approach, and this is thought to be due to the muscle-sparing aspect of the approach [19, 20]. Compared with the posterior approach, the anterior approach involves less exposure of the femur for medullary reaming, and this may pose problems with regards to femoral component positioning and femoral shaft complications [21].

## Methods

### Experimental design

This is a randomised controlled trial conducted at one site, Western Health, Melbourne Australia. There will be 243 patients recruited across three trial arms. Consultant orthopaedic surgeons will be performing or directly supervising all surgery. The research design is a stratified block permuted randomisation and is non-blinded. We are expecting to recruit 243 patients in 24 months based on institutional case load. The total time of this study will be 5 years.

The trial will be registered, constructed and presented according to the recommendations of the CONSORT statement [22, 23], the trial protocol and manuscript has been prepared in accordance with the SPIRIT checklist (Additional file 1 and Fig. 1).

**Fig. 1 Fig1:**
[figure not shown]
SPIRIT figure: trial timeline for recruitment, intervention, assessment and follow-up. OA, osteoarthritis; OHS, Oxford Hip Score; VAS, visual analogue scale

### Participants

Patients currently on the orthopaedic surgery waiting list at Western Health for a primary total hip arthroplasty will be invited to participate in the study. Patients referred to the clinic will be prospectively recruited prior to joining the waiting list and, once agreeable, will be randomised. Attendance at clinic is mandatory prior to surgery. Patients will undergo health assessment and provide informed consent to total hip arthroplasty. The department comprises consultant orthopaedic surgeons, orthopaedic registrars, resident medical officers and nursing and allied health staff. After initial screening, suitable patients will be a given a statement in plain English detailing the nature of the study and the commitment required. The consultant surgeon, research associates or resident medical officers will obtain informed consent for the study from suitable patients.

### Inclusion criteria

All adult patients (>18 years) who are on the waiting list for primary total hip arthroplasty will be considered eligible for the trial, unless they meet one of the exclusion criteria. This trial will include patients who have secondary osteoarthritis that could be post-traumatic, osteonecrosis or secondary to inflammatory arthropathy.

### Exclusion criteria

Patients who are having revision surgery or have indications for hip replacement other than osteoarthritis (i.e., fracture, malignancy, development dysplasia) will be excluded from the trial. Patients who are unable to complete the patient-reported outcome measures required, e.g., for mental health reasons or illiteracy, will be excluded from the trial.

### Intervention

Patients will be recruited from the Orthopaedic Outpatient Department at Western Health. Eligibility to participate will be assessed and patients will be asked to consent to enrol in the study. They will then be allocated to one of the three trial arms (anterior, lateral and posterior) and blinded to the allocation.

Operating surgeons will perform the approach that they are most familiar with using and the component system that they are most familiar with, to ensure that the study is not influenced by poor outcomes associated with surgeons performing approaches or components that they are not familiar with, e.g., Mr A, Mr B and Mr C will perform anterior approach total hip arthroplasty, Mr B, Mr D and Mr E will perform Hardinge approach total hip arthroplasty and Mr F, Mr G and Mr H will perform the posterior approach total hip arthroplasty. Nine surgeons will be involved in the study.

Pre-operatively the patients and the research team will be blinded to their allocation, whilst the treating surgeon will not be. However, blinding of the patients post-operatively will be impossible, owing to the nature of the incisions for the different approaches for hip arthroplasty.

### Standard of care

The components used will have the same design philosophy, with all patients receiving an uncemented acetabular component and anatomical shaped uncemented femoral stem or cemented femoral component. Sub-analysis will be performed between the cemented and uncemented stems. All patients will be subject to a standardised intraoperative and post-operative care protocol, including the use of tranexamic acid and local infiltration anaesthesia.

All patients will receive the standard routine post-operative management protocol of a wound review at 2 weeks, a further review with X-ray at 6 weeks and further information collected at 6, 12 and 24 months. Post-operative rehabilitation and physiotherapy will be standardised according to our institutional protocol and initiated for all patients at day 1 post-operatively (Fig. 2).

**Fig. 2 Fig2:**
[figure not shown]
Trial flow pathway. OHS, Oxford Hip Score; THA, total hip arthroplasty; VAS, visual analogue scale

### Outcome assessments

#### Data capture

Data will be captured by the research associates and resident medical officers. All information on general medical, operative and device-related complications will be documented and tabulated utilising the secondary outcomes listed in this paper. Our clinic routinely collect patient-reported outcome measures; the collection of this information will not involve deviation from our standard of practice.

#### Primary outcome

The primary outcome measure for this study is the Oxford Hip Score; this will be recorded as shown in Fig. 1 at the following time points: pre-operatively and post-operatively at 6 weeks, 6, 12 and 24 months. The primary outcome measure for which our study is powered is the Oxford Hip Score at 24 months.

#### Secondary outcomes

Secondary outcome measures will be recorded as follows:Complications° Dislocation rates° Infection rates° Intraoperative and periprosthetic fracture ratesComponent position° Leg length discrepancy, offset, acetabular cup positionLength of stayVisual analogue scale° If residual pain persists, the region of pain will be recorded as either buttock, trochanteric region or groin

#### Measurement tools

The measurement tools for this study are patient-reported outcome measures, specifically the Oxford Hip Score and a visual analogue scale for rating pain.

All information on general medical, operative and device-related complications will be documented and tabulated using the following clinical report forms:DemographicsPast historyBody mass indexMedical comorbidities, including cardiorespiratory disease, malignancy, obesity, diabetes mellitus and smoking statusKellgren–Lawrence grade of osteoarthritis on plain radiographsSurgical approachProsthesis usedComplications or adverse event, specifically looking for:° Infection of hip joint° Dislocation of hip joint° Intraoperative fracture or periprosthetic fracture post-operativelyProtocol deviationStudy termination

All information on complications or adverse events (date of occurrence, description, severity, related to study device, treatment and resolution) will be recorded at the time of occurrence.

Collection of the outcome scores will be blinded, with the investigators or researchers involved in the collection of the scores blinded to the allocation.

### Timelines

This trial will be conducted over 5 years; we anticipate 3 years of recruitment and 2 years of follow-up for each patient. Figures 1 and 2 provide the time points at which patients will be seen and data recorded.

### Recruitment

All patients presenting to the Western Health outpatient clinic during the recruitment period and placed on the waiting list for primary total hip arthroplasty will be invited to participate in the study, providing that they do not meet any exclusion criteria. The senior author and principal investigator will oversee recruitment.

### Data management

The research information will be re-identifiable. This means that we will remove the participants’ names and give the research information a special code number. Only the research team can match the participants’ name to their code numbers, if it is necessary to do so.

All electronic data will be kept secure by being accessed on computer via password only. A nightly back-up performed on the computer will ensure all data are safely and securely stored. Any hardcopy of data will be identified by number only and kept secure in a locked filing cabinet. All information will be stored in the research office at Western Health. Only the named researchers will have access to the information.

In presentations or publications arising from this study, information will be provided in such a way that participants cannot be identified. Data will be presented as grouped data. All analysis is anticipated to be completed and published within 3 years of completing data collection.

### Statistical considerations

The null hypothesis for this study is that patient-reported outcomes following three different approaches for total hip arthroplasty are no different when directly compared 24 months post-procedure. In addition we hypothesise that complication rates are the same between approaches. There is no randomised controlled trial that directly compares these three approaches for total hip arthroplasty. We are hence designing our study as a superiority study, looking for a significant difference in Oxford Hip Score and visual analogue scale rating between the different trial arms.

#### Randomisation and enrolment

The randomisation list will be computer-generated by an independent statistician. A stratified block permuted randomisation will be used with the Kellgren–Lawrence grading scale (grade 0–2 vs. grade 3–4) as the stratification variable [24]. The block size will not be disclosed, to ensure concealment. Randomisation will be enabled through a secure, web-based application.

The surgeons performing the operation will be assigned to an operation type according to their expertise. Each surgeon will perform a single operation type and each operation type will be conducted by three surgeons.

A patient will be managed by one of the three surgeons corresponding to the treatment group the patient is randomly assigned to. It is anticipated that each surgeon will treat roughly the same number of patients.

The study will enrol a total of 243 patients to be treated by nine orthopaedic surgeons at Western Health; this accounts for approximately 81 patients per operation type.

#### Sample size

Sample size is computed on the basis of our primary hypothesis that at least one of the three surgical methods will be superior to one other surgical method for total hip replacement, as measured by the change from pre-operation to 24 months post-procedure in the overall Oxford Hip Score. The minimal clinically important difference is at least five points and the best estimate for the standard deviation is nine points [25–28]. To control for the Type I error rate due to three treatment comparisons, a Holm–Bonferroni multiplicity adjustment will be used (i.e., a two-sided significance level of 0.0167 instead of 0.05). Using a two-sample *t* test, this leads to a sample size of 70 patients per operation type to obtain 80% power. This sample size needs to be increased because of two factors. Each surgeon will only perform one surgical method and as a result each patient cannot be assumed to generate independent observations because patients are clustered by surgeon. As a result, the sample size is inflated by 2.2% (i.e., a factor [1 + (*m* − 1) × intracluster correlation coefficient]) to achieve the variance that would have been anticipated had there been no clustering, assuming that each surgeon will treat 23 (*m* = 23) patients and the intracluster correlation coefficient is 0.001 [29, 30]. In addition, a drop-out rate of 10%, which includes a mortality of 2%, is anticipated at 24 months post-procedure [31], leading to an additional 11.1% increase in sample size.

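### The stated 80% power comes from a patient-level t test, but the planned surgeon-robust analysis has only nine surgeons; at a valid level, unadjusted power per contrast is about 55% (42% to 63%)

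*Protocol article*

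**What the plan says.** The Sample size section sets out the target: "The minimal clinically important difference is at least five points and the best estimate for the standard deviation is nine points". For three pairwise comparisons it uses "a two-sided significance level of 0.0167 instead of 0.05", and reports that "this leads to a sample size of 70 patients per operation type to obtain 80% power".

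It accepts that patients of one surgeon are not independent, so "the sample size is inflated by 2.2" per cent, with the stated purpose "to achieve the variance that would have been anticipated had there been no clustering". The inputs to that step are a cluster size, "assuming that each surgeon will treat 23", and a correlation: "patients and the intracluster correlation coefficient is 0.001". A 10% drop-out allowance follows.

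Randomisation and enrolment fixes the clusters: "The study will enrol a total of 243 patients to be treated by nine orthopaedic surgeons at Western Health", with three surgeons for each operation type and one operation type for each surgeon. Data analysis then specifies a repeated-measures mixed model, adjusted for the pre-operative Oxford Hip Score and its interaction with visit, with robust standard errors to allow for clustering by surgeon. The article states no df and no small-sample correction.

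**The concern.** Surgeon is fully nested in operation type. A test that estimates between-surgeon variation from the data, as robust standard errors do, draws its precision from the number of surgeons. Nine surgeons in three arms leave 6 df for a pooled surgeon-level comparison. The two compared arms alone leave 4, and the most generous convention (clusters minus one) gives 8. The design factor says how much the variance of an arm mean grows. It says nothing about how poorly that variance is estimated from so few surgeons, and so nothing about the larger critical value that is needed.

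The planning calculation and the declared analysis therefore describe different tests. If the 80% is carried into the report, a non-significant contrast will be read as coming from a trial well able to detect a 5-point difference, when the planned type of analysis, run at its nominal level, may have had much less chance of doing so.

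**Working it through.** **Inputs.** Difference 5, SD 9, two-sided alpha 0.0167 per contrast, intracluster correlation (ICC) 0.001 and drop-out 10% (Sample size); 81 patients and three surgeons per arm (Randomisation and enrolment). Evaluable patients per arm: 81 × 0.9 = 72.9, or 24.3 per surgeon. The example in the Intervention section lists one surgeon under two approaches; this check follows Randomisation and enrolment, where each surgeon performs one.

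**1. The plan's own figure.** A noncentral t calculation with 2n − 2 df gives 79.8% at n = 69 and 80.5% at n = 70, so 70 per arm reproduces. The design factor is 1 + 22 × 0.001 = 1.022. Then 70 × 1.022 = 71.5, and 71.5 / 0.9 = 79.5, so 80 per arm against 81 stated (81 = 3 × 27). The arithmetic is sound for a patient-level test.

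**2. Standard error with clustering.** Design factor: 1 + 23.3 × 0.001 = 1.0233. SE = 9 × √(2 × 1.0233 / 72.9) = 1.508. Noncentrality: 5 / 1.508 = 3.32.

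**3. Critical values and power at ICC 0.001.**

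| Reference df | Critical value | Power per contrast |
|---|---|---|
| 4 (two compared arms) | 3.96 | 41.9% |
| 6 (nine surgeons minus three arms) | 3.29 | 55.4% |
| 8 (clusters minus one) | 3.01 | 62.7% |
| about 144 (patient level) | 2.42 | 81.3% |

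Simulated surgeon means (400,000 runs, 24 evaluable patients per surgeon) gave 54.8% for the 6-df test, with null rejection of 1.7%. The chance that at least one of the three contrasts is significant was 56% for arm means 0, 2.5, 5 and 67% for 0, 0, 5.

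**4. Dependence on the ICC.** Values above 0.001 are assumptions. The last column is the difference detectable with 80% power at 6 df.

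| ICC | 4 df | 6 df | 8 df | Patient-level df | Detectable, 6 df |
|---|---|---|---|---|---|
| 0 | 42.8% | 56.5% | 63.9% | 82.3% | 6.4 |
| 0.001 | 41.9% | 55.4% | 62.7% | 81.3% | 6.5 |
| 0.01 | 35.0% | 46.8% | 53.5% | 72.5% | 7.1 |
| 0.02 | 29.5% | 39.6% | 45.5% | 63.7% | 7.8 |
| 0.05 | 19.9% | 26.5% | 30.5% | 44.6% | 9.4 |

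Even at ICC 0 the 6-df power is 56.5%. At the plan's ICC, the loss comes from the df and not from the correlation.

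**5. Uncorrected robust standard errors.** In the same simulation, a sandwich standard error with a normal reference rejected in 89% of runs at a true difference of 5. Under the null it rejected in 12.2% of runs per contrast against 1.67% nominal, and in 27% for any of the three. Referring the uncorrected standard error to 8 df still gave 6.9% per contrast. The apparent power is bought with type I error.

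**6. Baseline adjustment.** If SD 9 is the SD of change and the pre- and post-operative variances are equal, the adjusted SD is 9 × √((1 + r) / 2), where r is the pre/post correlation. The documents give no r. For r = 0.2, 0.5 and 0.7 (assumptions) the SD is 7.0, 7.8 and 8.3. At ICC 0.001, power is then 80%, 69% and 63% with 6 df, and 64%, 54% and 49% with 4 df.

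**The case against.** The strongest reply is that the 80% is right on the plan's own assumption. If the ICC really is 0.001, an ordinary patient-level test is almost unaffected by clustering: in simulation it rejects 1.8% under the null against 1.67% nominal, with about 82% power. This stands. A reader might infer that the sample size contains an arithmetic error, or that 80% is false at the plan's inputs; the documents do not support that. But the patient-level test is not the planned one. Data analysis has clustering estimated from the data, and the patient-level test loses its level if the ICC is larger (null rejection about 3% at 0.01 and 10% at 0.05, both assumed).

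Second, df may be settled in an analysis plan that is not shown. That is fair, so no missing df method is charged here. The point concerns a power figure that the protocol does fix, and each of 4, 6 and 8 df contradicts it before baseline adjustment.

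Third, the specified model adjusts for baseline, which the figures in steps 3 and 4 leave out. This also stands. It is why 55% should not be read as the power the trial delivers, and why a claim that it would miss a 5-point difference almost half the time is not established. The protocol, however, does not rest its 80% on any such gain, and at 6 df the gain reaches 80% only at the low end of the assumed correlations.

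Two further inferences fail. The cluster size of 23 does not conflict with 243 / 9 = 27: 70 / 3 = 23.3 is evaluable patients per surgeon before inflation and 27 is randomised patients, and the design factor barely moves (1.022 against 1.026). Nor is it true that a non-significant result could never exclude 5 points. At 6 df the 98.33% interval has a half-width of about 3.29 × 1.508 = 4.96, so an estimate near zero would typically just exclude it.

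**Conclusion.** The point holds as a mismatch between the power calculation and the declared analysis. For a surgeon-based test that keeps its level, unadjusted power per contrast at the plan's inputs is about 55% with 6 df, within a range of 42% (4 df) to 63% (8 df), against 80% stated. The detectable difference at 6 df is about 6.5 points, against the 5 points targeted.

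These figures assume three equally loaded surgeons per arm, 72.9 evaluable patients per arm, SD 9 and ICC 0.001. They worsen with a larger ICC and improve with baseline adjustment, by an amount the documents do not allow one to fix. Nothing in the protocol plans an equivalence reading: it declares superiority and commits to confidence intervals. Over-interpretation of a null result is therefore a risk to guard against in the wording, not something the plan proposes.

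**What to change.** In the Sample size section, restate power as that of the surgeon-clustered analysis with a small-sample df reference:

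- Show it as a range over df (4, 6, 8) and ICC (for example 0.001 to 0.05, with values above 0.001 labelled as assumptions).
- Give the detectable difference beside it.
- Report any gain expected from baseline adjustment separately, with the assumed pre/post correlation and whether SD 9 refers to change.
- Add that non-significance alone is not evidence of equivalence, and that the 98.33% confidence interval decides whether a 5-point difference is excluded.

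The change is to wording only. It asks for no extra patients and leaves the cluster size of 23 as it is. Its one cost is a less favourable stated power.
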